### Group interventions

#### *The study group (tDCS* + *WMT)*

Based on previous findings [28, 29], we will apply tDCS at 2 mA for 20 min each, with two stimulations per day separated by 3–4 h. Stimulation will be performed 5 days per week for two consecutive weeks, for a total of 20 stimulations.

We will administer tDCS using a battery-driven stimulator (EM8060, Wuhan YiMai Technology Co., Ltd., Hefei City, China) in Beijing center and a-tDCS (ActivaDose® II, ActivaTeKTM Inc., Gilroy, CA) in Chongqing center. A rectangular anodal electrode will be attached to the left DLPFC (F3 position, according to the International 10/20 system), and a rectangular cathode will be attached to the orbitofrontal cortex. The stimulation area will be wet with saline before treatment.

Each 20-min tDCS period will be immediately followed by a 1–2-min rest and 40 min of WMT (Fig. 2). The WMT tool is a computer training system based on theoretical models of working memory and cognitive processing. It was self-developed and validated in preclinical research [30]. This training employs the most typical working memory paradigm; that is, subjects try to memorize a series of continuous items (including numbers, words, and pictures) of random (unfixed) length, and judge the order of the 2–4 items presented at the end. Ten WMT sessions will be performed per week for two weeks, for a total of 20 WMT sessions.

**Fig. 2 Fig2:**
[figure not shown]
The tDCS + WMT group

#### *The WMT control group (tDCS* + *SRT)*

The tDCS stimulation protocol is the same as that described in the previous section. Subsequently, SRT will be performed (Fig. 3). SRT requires no working memory processing; thus, it can be used as a comparison condition for WMT. During SRT, the patient must press a key (space) when a specific shape (such as a red triangle) is presented among many sequentially presented geometric figures. To avoid the influence of the individual items on the results, the items of the SRT are the same as those used in the WMT training,

**Fig. 3 Fig3:**
[figure not shown]
The tDCS + SRT group

#### *The tDCS control group (sham tDCS* + *WMT)*

During each treatment period, the patient will receive 20-min sham tDCS. The stimulation position and parameters, as well as the electrode placement, are identical to those utilized for the tDCS protocol. Electrical stimulation will be administered for only 40 s, and subsequently, its intensity gradually decreases to 0. After a short interval (1–2 min), the patients will undergo WMT with the same training method and duration as the study group (Fig. 4).

**Fig. 4 Fig4:**
[figure not shown]
The sham tDCS + WMT group

#### *The placebo control group (sham tDCS* + *SRT)*

During each treatment period, the patients will receive 20-min sham tDCS. After a short interval (1–2 min), simple reaction training will be performed (Fig. 5).

**Fig. 5 Fig5:**
[figure not shown]
The sham tDCS + SRT group

### Outcome measures and assessment

The primary outcome measure is cognitive function measured using Repeatable Battery for the Assessment of Neuropsychological Status (RBANS) and some subscales of the MATRICS Consensus Cognitive Battery (MCCB). Secondary outcomes are behavioral changes, modifications in brain structural and functional plasticity as measured by MRI, and serum levels of BDNF. All participants from both hospitals will be assessed by neuropsychologists with considerable training.

### Data collection and follow-up

Investigators will visit the participants before the beginning of the trial (baseline), at the end of the trial, and 3 months after the last treatment. Calls will be required to keep in touch with the patients and remind them of their next interview to avoid loss to follow-up.

Baseline demographic data (age, sex, education, occupation, etc.), smoking status, current medication, concomitant medications, detailed physical and neurological findings, functional and structural brain MRI, the serum BDNF assay, and neuropsychological data will be collected. A follow-up assessment will be scheduled post-treatment and three months after the last cognitive training. Neuropsychological assessments will be performed post-treatment and at the three-month follow-up. Functional and structural brain MRI and the serum BDNF assay will be also performed post-treatment (Fig. 6).

**Fig. 6 Fig6:**
[figure not shown]
The treatment flowchart

### Neuropsychological assessments

Cognitive function will be measured with RBANS and some subscales of the MCCB and the Wechsler Adult Intelligence Test Brief Version (WAIS-R). The primary evaluation indicators of a training effect on working memory are the spatial span and digital sequence subscales in the MCCB and the RBANS. Evaluation indicators of the migration effect are reasoning and problem solving ability evaluated by the maze test and social cognition ability determined by the vocal emotion recognition test (VERT) and facial emotion recognition test (FERT).

Clinical symptoms will be evaluated using the Chinese version of the PANSS, Brief Negative Symptom Scale (BNSS), and Clinical Global Impression (CGI). These will be assessed by four clinically trained senior physicians at each center.

Social function will be determined with the Personal and Social Performance Scale (PSP). Other scales employed are the Temporal Experience of Pleasure Scale (TEPS), Self-Esteem Scale (SES), and side effects scale*.*

The results from the above mentioned neuropsychological tests will be blindly assessed by raters who are unaware of the treatment the patients are receiving. Except for the WAIS-R, which will be assessed only once at baseline, the other scales will be assessed at three time points (baseline, post-treatment, and 3-month follow-up).

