### Data management and monitoring

The data will be kept strictly confidential and stored in the Alibaba Cloud through eCRF. Every member of the team will create a personal account for data entry and modification. A correction function will be run in the background of eCRF to prevent errors. The data sets and informed consent forms analyzed during the current study are available from the respective authors upon reasonable request.

A project management team is created to supervise the overall work of the two centers. The trial review team consists of two staff members from the review department and is responsible for a regular review of progress, authenticity, and safety every 6 weeks.

The intervention may produce mild adverse events such as headaches and irritability, which can be improved by providing patients with rest or interval stimulation. If patients showed intolerance, they could opt out of the trial. This situation should be reported to the supervisory department. Trial audit teams, independent data monitoring, and ethics committees must review the conduct throughout the trial.

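### The side-effects scale is scheduled only at baseline, post-treatment and 3 months, a poor fit for the session-related effects the protocol expects

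*Protocol article*

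**What the plan says.** The protocol article introduces the instrument under Neuropsychological assessments: "Other scales employed are the Temporal Experience of Pleasure Scale (TEPS), Self-Esteem Scale (SES), and side effects scale". The timing rule comes at the end of the same section. It opens with its one exemption, "Except for the WAIS-R, which will be assessed only once at baseline", and continues that "the other scales will be assessed at three time points (baseline, post-treatment, and 3-month follow-up". The side-effects scale is not exempted. It has no name, and neither its content nor its recall period is given.

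The visit schedule under Data collection and follow-up agrees: "Investigators will visit the participants before the beginning of the trial (baseline), at the end of the trial, and 3 months after the last treatment".

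Treatment is described under the study group: "Stimulation will be performed 5 days per week for two consecutive weeks, for a total of 20 stimulations".

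Data management and monitoring states which harms are expected: "The intervention may produce mild adverse events such as headaches and irritability, which can be improved by providing patients with rest or interval stimulation". It adds that patients who cannot tolerate treatment may leave and that this is reported to the supervisory department. A review team carries out a "regular review of progress, authenticity, and safety every 6 weeks".

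**The concern.** Effects that settle with rest or with spacing of stimulation arise around single sessions. A scale given before the course, after it and 3 months later is timed for lasting change in cognition or symptoms, not for a headache that comes and goes in the first week.

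Two things are at stake. First, any description of tolerability under active versus sham stimulation may rest on ratings taken when most session-related effects have passed. If both arms are under-recorded in this way, a real difference between them would tend to shrink. Second, the Discussion names as open questions whether patients will find treatment unpleasant or exhausting, whether they can tell real from sham, and what this does to attrition. Ratings close to the sessions would be direct evidence on discomfort and useful evidence on the rest. Patients who leave early because of discomfort are the most informative, and under this schedule they may have a baseline rating and nothing from the treatment period.

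**Working it through.** **Inputs from the protocol article.** Two stimulations per day, 5 days per week, 2 weeks (study group section). Three time points for the scale (Neuropsychological assessments). Four groups of 30, 120 patients in all (Sample size).

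**The plan's own figure.** 2 × 5 × 2 = 20 stimulations, over 5 × 2 = 10 treatment days. This agrees with the stated total of 20.

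**Ratings set against sessions.**
- Before stimulation 1: one rating (baseline).
- Between stimulation 1 and stimulation 20: none scheduled.
- After stimulation 20: one rating (post-treatment). The article does not say whether this falls on the last treatment day.
- Three months later: one rating, too late to observe effects tied to a session.

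**What a current-state rating could catch.** The documents give no event rate, so the per-session risk p below is an assumption, shown over a range. Sessions are taken as independent.
- Any event over the course: 1 − (1 − p)^20
- Any event on the last treatment day (two sessions): 1 − (1 − p)^2
- Event at the last session alone: p

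| Assumed p | Any of 20 sessions | Last day (2 sessions) | Last session | Last day ÷ any |
|---|---|---|---|---|
| 2% | 33% | 4% | 2% | 12% |
| 5% | 64% | 10% | 5% | 15% |
| 10% | 88% | 19% | 10% | 22% |
| 20% | 99% | 36% | 20% | 36% |

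Even if the post-treatment rating falls on the last day and picks up both sessions of that day, a form asking only about the present would find between about one in eight and just over one in three of the patients ever affected.

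The independence assumption sets the size of this gap. If the same patients were affected at every session, the last session would identify all of them and the gap would close. If effects were concentrated in the early sessions, the gap would be wider than in the table. A post-treatment form that asks about the whole two weeks would also narrow it, subject to recall. Recall is a weak basis here because evidence of cognitive impairment is an inclusion criterion (Participants).

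**Early stoppers.** The dropping criteria (Participants) include failing to complete ten trainings. The article schedules no side-effect rating at discontinuation, so a patient who leaves in the first week may have only the baseline rating.

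**What is not touched.** The scale plays no part in the sample size calculation or in the primary analysis, so there is no power or sample size figure to recompute.

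**The case against.** The strongest reply is that the instrument is unidentified. It stands beside pleasure and self-esteem scales, these patients take medication, and a general or drug side-effects scale would suit three visits. If the post-treatment form asks about the whole course, it covers the two weeks by recall. This stands, and it is why the point is conditional on the recall period.

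A reader might go further than the documents allow in four ways:

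- **That adverse events during treatment go unrecorded.** The text does not support this. Easing events by rest or spacing presupposes that staff notice them, intolerance is reported, and oversight bodies review the conduct of the trial. An adverse-event log is the kind of detail an article leaves to the full protocol, and the schedule figure is not shown.
- **That the scale will read near zero at every visit, or that all 60 × 20 = 1,200 active stimulations (two active groups of 30) go unrated.** Both need a current-state form, and the first also needs every effect to have resolved. Neither condition is established.
- **That a planned comparison is biased.** The article names no tolerability outcome and states no active-versus-sham tolerability analysis. What would suffer is a description, if one is given.
- **That the 6-week safety review leaves the gap open because it spans 6 ÷ 2 = 3 course lengths.** It is an oversight cycle over continuing enrolment and has no bearing on when the scale is given.

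A further objection concerns the remedy. Under Randomization and blinding, the caregivers who give tDCS are the only people who know the allocation. Daily ratings taken by them could differ between active and sham for that reason alone. This also stands, and the fix allows for it.

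The objection does not remove the stated timing. The article does not leave the schedule of this scale open: it fixes it, with a single exemption that does not apply.

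**Conclusion.** The point holds as a matter of timing. The stated schedule places no administration of the side-effects scale within the 20-stimulation course, although the effects the article expects are tied to sessions. Unless the post-treatment form covers the full two weeks, tolerated or resolved effects are likely to be under-recorded, and patients who stop early may contribute no on-treatment rating. That weakens any description of tolerability by arm and the evidence on the article's own question about discomfort and attrition.

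The size depends on assumptions. For independent per-session risks of 2% to 20%, a current-state rating on the last day would find about 12% to 36% of the patients ever affected. Clustering within patients or a retrospective form would make the loss smaller. No primary result, sample size or power is affected. This is a cheap improvement to the tolerability data. It is worth making before recruitment starts, because ratings taken close to the sessions cannot be recovered afterwards.

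**What to change.** Exempt the side-effects scale from the three-visit rule and name the instrument. Then:

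- Have patients complete a short version themselves on each treatment day after the second session, and at discontinuation if they stop early.
- Keep the baseline and post-treatment ratings, and state a recall period for the post-treatment form that covers the whole treatment course.
- Do not have the form rated by the caregivers who give tDCS, since they know the allocation. Keep completed forms away from the outcome raters, because reported sensations could suggest the arm.
- Report by arm the number of patients with any event and the worst severity per patient.

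This changes only what is measured: no treatment rule and no part of the efficacy analysis is altered. The cost is a few minutes per patient per day, up to 10 × 120 = 1,200 short forms, one added eCRF page and a protocol amendment.

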### MRI protocol

Brain MRI will be performed at Beijing Huilongguan Hospital. Due to limited experimental conditions, patients of Chongqing Three Gorges Hospital will not undergo MRI.

Patients will undergo a brain MRI at baseline and after treatment. MRI will be performed using an optimized protocol with a 3.0-T MRI scanner (Siemens Healthcare, Prisma, Germany). The fMRI data will be analyzed using statistical parametric mapping (SPM) (UCL Queen Square Institute of Neurology, London, UK). Changes in brain activation and connectivity between baseline and post-treatment will be compared between the four groups.

### Blood sampling

Serum samples will be obtained to analyze BDNF levels at baseline and post-treatment. Peripheral venous blood (10 mL) will be collected from 7:00 am to 9:00 am in a climate-controlled room following overnight fasting. Blood samples will be centrifuged at 4000 g for 15 min at 4 °C. Serum and plasma will be separated and stored at − 80 °C. Serum levels of BDNF will be measured using enzyme-linked immunosorbent assay (ELISA) kits (R&D Systems, Minneapolis, MN, USA).

All samples will be measured by the same technician who is blinded to the patient treatment status. All samples will be evaluated in duplicate and averaged.

### Data management and monitoring

The data will be kept strictly confidential and stored in the Alibaba Cloud through eCRF. Every member of the team will create a personal account for data entry and modification. A correction function will be run in the background of eCRF to prevent errors. The data sets and informed consent forms analyzed during the current study are available from the respective authors upon reasonable request.

A project management team is created to supervise the overall work of the two centers. The trial review team consists of two staff members from the review department and is responsible for a regular review of progress, authenticity, and safety every 6 weeks.

The intervention may produce mild adverse events such as headaches and irritability, which can be improved by providing patients with rest or interval stimulation. If patients showed intolerance, they could opt out of the trial. This situation should be reported to the supervisory department. Trial audit teams, independent data monitoring, and ethics committees must review the conduct throughout the trial.

### Statistical analysis

Analyses will be performed according to the intent-to-treat (ITT) principle. Descriptive analysis will be performed on the data collected during each assessment at baseline, post-treatment, and the 3-month follow-up. The median and range describe continuous variables, and the frequencies and percentages describe qualitative variables.

Statistical significance will be set at *P* < 0.05, and corrected for multiple comparisons, when needed. To assess our primary endpoint criterion, that is, changes in cognitive performance, the outcomes at the three time points will be compared using a repeated-measures analysis of variance (ANOVA) with time (baseline, post-treatment, and 3-month follow-up) and group (tDCS + WMT, tDCS + SRT, sham tDCS + WMT, and sham tDCS + SRT) as factors. Further comparisons between the two groups can show the simple tDCS effect, simple WMT effect, and promoting effect of tDCS on WMT. Sensitivity analyses will be used to explore the effect of missing data due to loss to follow-up and dropout.

In cases where the data do not satisfy the assumption of normal distribution, the non-parametric Mann–Whitney *U* test will be used to compare the performance improvement between the four groups. SPM will be used to analyze imaging data to detect changes in brain function caused by cognitive training.

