## Abstract

**Background:**

Working memory deficits are one of the core and most characteristic clinical features of cognitive impairment in schizophrenia. Cognitive training can improve the cognitive function of patients with schizophrenia. However, the overall and transfer effects of working memory treatment (WMT) require improvement. Numerous studies have confirmed that transcranial direct current stimulation (tDCS) enhances neuroplasticity in the brain, providing a new treatment approach for cognitive impairment in patients with schizophrenia. We hypothesize that a training mode combining “preheating” (tDCS, which changes the neural activity of working memory-related brain regions) and “ironing” (WMT) affords greater cognitive improvements than WMT alone. In addition, this study aims to examine the mechanisms underlying the superiority of tDCS combined with WMT in improving cognitive function in patients with schizophrenia.

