## Methods

### Study design

This is a double-center, double-blinded, randomized, controlled intervention trial. This study was registered under Chictr.org.cn (ChiCTR2200063844). This study will be conducted from 2022 to 2024 and reported in accordance with both the Consolidated Standards of Reporting Trials (CONSORT) statement and the CONSORT statement for non-pharmaceutical interventions [24, 25].

The primary objective of this trial is to investigate the facilitation (enhancement) effect of tDCS-induced neuroplasticity changes on the direct and migratory effects of WMT on cognitive function in schizophrenia. The secondary goals are to investigate the effects of tDCS and WMT on the brain plasticity and biological markers of patients with schizophrenia, and to examine the facilitation effect of tDCS on WMT-induced changes in brain plasticity and biological markers.

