## Discussion

As far as we know, working memory deficits are one of the core features of cognitive impairment and are closely related to social function in patients with schizophrenia. Although current WMT methods can improve cognitive performance, their overall and transfer effects are relatively low. More effective methods are urgently required to enhance the effects of WMT. This study is the first to combine tDCS stimulation with WMT to enhance the effect of WMT, altering the neuroplasticity of related brain regions in patients with schizophrenia.

This study has several strengths. As a well-documented effective method for altering brain plasticity, tDCS stimulation is used to modulate the functional state of brain regions prior to WMT, and functional MRI is used to explore the effects of tDCS on brain functional plasticity in patients with schizophrenia. In addition, a key issue for WMT mechanism studies is determining whether tDCS stimulation first activates local neuronal activity, subsequently enabling WMT to produce more pronounced changes in brain function. To determine this, we compare the tDCS + SRT and sham tDCS + WMT groups to explore whether the tDCS combined with the WMT approach would be superior to either in altering neuroplasticity (function and structure). Our findings help to confirm our hypothesis that tDCS can facilitate the clinical effect of WMT on cognitive improvement in schizophrenia and provide a scientific basis for exploring ways to enhance brain neuroplasticity and improve its function. Another strength of this trial is the exploration of the transfer effect, as our data will determine whether training, such as WMT, can improve untrained cognitive ability, including logical reasoning. The transfer effects of WMT on healthy individuals have already been confirmed, but few studies have investigated whether such effects also occur in schizophrenia. This study will fill this gap in knowledge.

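### No two-group comparison can show that tDCS promotes WMT: a purely additive tDCS effect can pass for facilitation unless the tDCS × WMT contrast is prespecified

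*Protocol article*

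**What the plan says.** The protocol article states its aim in two strengths. Under Study design the primary objective is to "investigate the facilitation (enhancement) effect of tDCS-induced neuroplasticity changes on the direct and migratory effects of WMT on cognitive function in schizophrenia". The Abstract's hypothesis is weaker: the combined mode "affords greater cognitive improvements than WMT alone".

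The Statistical analysis section plans a repeated-measures ANOVA with time (three visits) and "group (tDCS + WMT, tDCS + SRT, sham tDCS + WMT, and sham tDCS + SRT) as factors". It continues: "Further comparisons between the two groups can show the simple tDCS effect, simple WMT effect, and promoting effect of tDCS on WMT". If normality fails, the "Mann–Whitney *U* test will be used to compare the performance improvement between the four groups". The section says that significance will be corrected for multiple comparisons when needed, without naming a method.

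The Discussion returns to the question for neuroplasticity: "we compare the tDCS + SRT and sham tDCS + WMT groups to explore whether the tDCS combined with the WMT approach would be superior to either". The article names no tDCS × WMT interaction and no difference of differences.

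**The concern.** Facilitation is effect modification: the gain from WMT is larger when tDCS precedes it. The four arms cross tDCS (active, sham) with training (WMT, SRT), so the design can identify this, but only by combining all four arms. The analysis text instead assigns the promoting effect to comparisons of two groups. This is a statement about what a contrast can show, and it is incorrect. It is not a detail left to an unseen analysis plan.

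At stake is the conclusion on the primary objective. If tDCS simply adds a fixed amount whichever training follows, the combined arm will tend to beat WMT alone, and the plan as worded allows that to be reported as tDCS promoting WMT. The clinical reading differs: an additive benefit would need no particular pairing of the two treatments.

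**Working it through.** **Inputs from the protocol article.** Allocation 1:1:1:1 (Randomization and blinding). 30 per group, alpha 0.05, power 0.90, effect size 0.25, 4 groups, 3 measurements, correlation 0.5, nonsphericity correction 1, minimum sample size 52 (Sample size).

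**Assumptions.** The article gives no SD and no expected tDCS effect. I take change-score SD 1, which equals a raw SD of 1 at correlation 0.5, since the variance of a change is 2(1 − 0.5) = 1. Additive tDCS effects of 0.3 and 0.5 SD are illustrations, with 0.8 SD as an upper case.

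**1. The plan's own figure.** For the group × time test, λ = N·m·f²/(1 − ρ), df1 = (4 − 1)(3 − 1) = 6 and df2 = (N − 4)·2. At N = 52, λ = 52 × 3 × 0.0625/0.5 = 19.5, df2 = 96, and power is 0.915. N = 48 gives 0.887; the smallest N reaching 0.90 is 50, which becomes 52 with equal groups. The stated 52 is reproduced, and it belongs to the omnibus group × time test.

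**2. Algebra.** Write mean changes as A = tDCS + WMT, B = tDCS + SRT, C = sham tDCS + WMT, D = sham tDCS + SRT. Let tDCS add t, WMT add w, and facilitation add g in the combined arm only, relative to D:

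- A − C = t + g
- A − B = w + g
- B − D = t
- C − D = w
- (A − C) − (B − D) = g

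The two remaining pairs do not isolate g either: A − D = t + w + g and B − C = t − w. Finding A versus C significant while B versus D is not does not test g. The Mann–Whitney fallback is also a two-sample test.

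**3. How often additivity passes for promotion (g = 0, 30 per arm).** For A versus C the noncentrality is t·√(30/2), with 58 df. At t = 0.5 it is 0.5 × 3.873 = 1.94; at t = 0.3 it is 1.16.

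| Additive tDCS effect | Change score, alpha 0.05 | Change score, alpha 0.05/3 | Baseline-adjusted (r = 0.5), alpha 0.05 | Baseline-adjusted, alpha 0.05/3 |
|---|---|---|---|---|
| 0.3 SD | 21% | 10% | 26% | 14% |
| 0.5 SD | 48% | 31% | 59% | 42% |

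Baseline adjustment is not in the plan; its residual SD is √(1 − 0.5²) = √0.75. At 0.8 SD the change-score figure at unadjusted alpha is 86%.

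In simulation with t = w and g = 0 (20,000 trials each, change-score SD 1), the combined arm beat both single-active arms in 9% (0.3 SD), 31% (0.5 SD) and 77% (0.8 SD) of trials. The interaction contrast rejected in 4.9% to 5.1%.

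The omnibus test does not separate the cases. With correlation 0.5 and effects present at both later visits, it rejected under pure additivity in 47% (0.3 SD) and 93% (0.5 SD) of 5,000 simulated trials.

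**4. Precision of the correct contrast.** SE(A − C) = σ√(2/30) = 0.258σ. SE(A − B − C + D) = σ√(4/30) = 0.365σ, a ratio of √2 = 1.41. With 116 df, the smallest interaction detectable at 80% power is 1.03 SD for change scores, or 0.89 SD if baseline-adjusted with r = 0.5. Power for a change-score interaction of 0.5 SD is 27%, and for 0.8 SD it is 58%.

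**The case against.** The strongest reply is that the hypothesis as the Abstract words it needs only tDCS + WMT against sham tDCS + WMT, and that promotion may mean no more than this added benefit. For the Abstract's hypothesis this stands: the comparison is a valid test. It does not cover the objective under Study design, which concerns an enhancement of WMT's effects. The analysis section also lists the promoting effect separately from the simple tDCS effect, so the authors treat them as different quantities.

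Several stronger readings are tempting, and the document does not support them:

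- *The single four-level group factor is a modelling error.* It is not. It is the same saturated model as tDCS, WMT and their interaction; the needed contrast is already inside it.
- *The six-degree-of-freedom test wastes power on effects nobody asked about.* It does not. The simple tDCS effect, the simple WMT effect and facilitation account for three between-group contrasts, and three visits give two time contrasts: 3 × 2 = 6.
- *An additive effect is bound to be reported as promotion.* It can be. The frequency depends on an assumed effect size, and the multiplicity correction the plan allows for would lower it, as the table shows.
- *The Discussion leaves the combined arm out of the comparison.* Read literally, "we compare the tDCS + SRT and sham tDCS + WMT groups to explore whether the tDCS combined with the WMT approach" does name only the two single-active arms. The words that follow make clear that the combination is to be compared with each. This is loose wording about neuroplasticity, a secondary outcome. Even so, superiority to each arm alone is not facilitation.

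**Conclusion.** The point holds for the primary objective. The statement that two-group comparisons can show promotion is wrong by algebra, whatever the effect sizes. The size of the risk does rest on assumptions: change-score SD 1, 30 analysed per arm, and an additive tDCS effect of 0.3 to 0.5 SD. On these, an additive effect would be significant in the key pairwise comparison in about 21% to 48% of trials unadjusted, or 10% to 31% with a Bonferroni correction for three comparisons, which is my illustration because the plan names no method. The interaction contrast keeps the error at 5%.

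The Abstract's hypothesis is unaffected. The sample size was not derived for facilitation, and with 120 patients only a large interaction is likely to be detected.

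**What to change.** 1. Keep the model. Prespecify, as the test of facilitation, the one-df contrast on change, (tDCS + WMT − sham tDCS + WMT) − (tDCS + SRT − sham tDCS + SRT), reported with its confidence interval. Allow claims of facilitation or promotion only on this contrast.
2. Keep tDCS + WMT against sham tDCS + WMT as the test of the Abstract's hypothesis, and label it added benefit.
3. Reword the Discussion so that superiority to either means the combined arm compared with each single-active arm.
4. State beside the sample size that 52 was calculated for the omnibus group × time test, and give the detectable interaction (1.03 SD, or 0.89 SD if baseline-adjusted with r = 0.5).

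This needs no new data, arms or visits, only wording and one contrast. The real cost is that facilitation becomes harder to claim: the standard error is 1.41 times that of the pairwise contrast, and at 90% power a change-score interaction of 0.5 SD would need about 676 patients in total. The interaction should therefore be presented as an estimate with its interval, and a non-significant result should not be read as absence of facilitation.
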